### Concealment mechanism {16b}

A research assistant (a postgraduate nursing student), who will not be involved in any session of the study, will place the randomized numbers in an opaque envelope and number them sequentially, then randomly assign the participants.

### Implementation {16c}

After consent and baseline assessment, eligible participants will receive sequentially numbered envelopes and will be assigned to either the intervention or control group based on the numerical number inside the envelope.

## Assignment of interventions: blinding

### Who will be blinded {17a}

The evaluator will blind to the assignment of all participants, and will not participate in the application of the treatment or the statistical analyses. Due to the specific nature of video-game interventions, it is not possible to blind participants and therapists.

### Procedure for unblinding if needed {17b}

N/A: Only outcome evaluators in this study will be blinded, so unblinding will not occur.

## Data collection and management

### Plans for assessment and collection of outcomes {18a}

Each participant will be assessed individually three times, pre-intervention, post-intervention and follow-up. The assessments will focus on swallowing function, quality of life, nutritional level and satisfaction with video games. Data will be collected by the investigators on site using case report form (CRF). All data obtained during the study will be anonymized and stored in folders in a protected research server at the Hong Kong Polytechnic University. Only the research team is allowed to access the folder.

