## Abstract

**Background:**

Dysphagia can lead to serious complications such as aspiration and aspiration pneumonia, timely and effective rehabilitation training can improve the swallowing function of patients. However, the conventional rehabilitation training methods used in clinical settings have shortcomings such as poor adherence of patients. We present the study design of a randomized controlled trial that evaluated whether video-game based swallowing rehabilitation training can effectively improve swallowing in patients with dysphagia and whether it has additional benefits compared with conventional training methods to improve swallowing function and training compliance among patients with dysphagia.

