### Strategies to improve adherence to interventions {11c}

Video-game based swallowing rehabilitation programs are safe with multiple game components, so high compliance with the program is expected. Adherence is based on the actual completion of the patient's swallowing function training. The actual completion of the dysphagia training by patients, including the number of training sessions completed and the duration of the training, is objectively recorded by the researcher. In addition to this, participants will be asked to complete a daily training diary in which they record the training activities they perform and record the duration, intensity, and symptoms of discomfort.

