### Provisions for post-trial care {30}

There is no anticipated harm and compensation for trial participation. Neither the measurements nor the game manipulation produces any significant harmful side effects, as the game does not have graphic depictions of violence, and any of our measurements are not invasive.

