### Outcomes {12}

All assessments were completed by an experienced occupational therapist who was blind to the participants' group assignments. Assessments were conducted before the start of the intervention (pre-training), after 4 weeks of treatment (post-training), and at the 1-month follow-up (follow-up).

The primary outcome of this study was swallowing function, assessed using the Toronto Bedside Swallowing Screening Test (TOR-BSST) and the Functional Oral Intake Scale (FOIS). The Toronto Bedside Swallowing Screening Test (TOR‐BSST) is the best performing water swallow screening tool [21] with a sensitivity of 91.3%, a negative predictive value of 93.3% in the acute phase and 89.5% in the recovery phase [22]. TOR-BSST has shown to be more convenient and cheaper in bedside screening compared to the gold standard method of simultaneous videofluoroscopy (VFSS), which is an invasive assessment. Due to the limitations of the experimental site, we chose TOR-BSST as the assessment tool for dysphagia. FOIS consists of a 7-point scale, with level 1 indicating completely impaired oral intake and level 7 indicating complete oral intake regardless of food concentration or type [23].

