### Adverse event reporting and harms {22}

Adverse events will be documented by the research coordinator. Minor adverse events such as fatigue will be recorded in the adverse event count form. A healthcare staff who is not involved in the study will accompany the participants during their training. Since the use of video games as an intervention method may cause discomfort such as visual fatigue in participants, the study will be stopped and observed immediately when participants experience any discomfort. If the discomfort is not relieved after half an hour, it will be immediately reported to the doctor in charge and relevant treatment will be given. Serious adverse events, such as fractures, and bleeding will be reported immediately to the Health Research Ethics Committee and discussed with the participant's doctor, who will provide medical follow-up if necessary. Participants may withdraw from the trial at any time.

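### Adverse events are to be documented, but no active ascertainment of aspiration or aspiration pneumonia, equal in both arms, is stated outside the training sessions, including weeks 5 to 8

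*Protocol article*

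**What the plan says.** The abstract opens with the complications that motivate the trial: "Dysphagia can lead to serious complications such as aspiration and aspiration pneumonia". The background section {6a} names them again.

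On collection, section {18a} states: "Each participant will be assessed individually three times, pre-intervention, post-intervention and follow-up". It then says: "The assessments will focus on swallowing function, quality of life, nutritional level and satisfaction with video games". Section {12} makes TOR-BSST and FOIS the primary outcomes. Quality of life, nutritional status, satisfaction and adherence are secondary. Neither list holds a harm item.

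On harms, section {22} begins with a general provision: "Adverse events will be documented by the research coordinator". It sets no period and no limit to sessions. The detection step it goes on to describe is specific: "A healthcare staff who is not involved in the study will accompany the participants during their training". Section {11c} adds a daily training diary in which participants "record the duration, intensity, and symptoms of discomfort".

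On expected risk, sections {11b} and {30} foresee no important harm from the game or the measurements, partly because "any of our measurements are not invasive". Section {12} says of TOR-BSST that it "is the best performing water swallow screening tool".

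**The concern.** FOIS grades oral intake, so a patient who is fed more by mouth scores higher. In a dysphagia population a reader will want to know whether a gain on FOIS came with more, fewer or the same number of aspiration events and chest infections. That needs the same questions, asked the same way and over the same period, in both arms.

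The article does not state such a step. What it does state leans on training sessions, and those end at week 4, whereas the trial runs to week 8. Pneumonia need not show itself in a 30-minute session.

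Section {17a} confirms that participants and therapists are not blinded. Spontaneous reporting can therefore differ by arm for reasons unrelated to the true event rate. Section {22} explains its stop-and-observe step by visual fatigue from video games, a reason that concerns one arm only.

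The safety reasoning also skips the obvious route of harm. A test that is not invasive can still involve swallowing water, and here it is given to patients selected because they swallow badly.

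**Working it through.** The point disputes no figure in the article, so the check is mainly a comparison of sections. The arithmetic at the end is context.

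**Where could an aspiration or pneumonia be picked up?**

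- *General documentation by the coordinator ({22}).* Not limited to sessions or to an arm. No window, definition or prompt is stated, so it is passive.
- *Accompanying staff ({22}).* Training only, hence weeks 1 to 4. Section {11a} adds that 17 of the 20 sessions are done independently by the patient, so what accompaniment means needs to be clear.
- *Diary ({11c}).* Linked to training, and records discomfort.
- *Weekly monitoring ({11d}).* Covers both groups. Its stated purpose is consistency of usual care.
- *Status monitoring during follow-up ({18b}).* Covers weeks 5 to 8. Its stated purpose is completing the study.
- *Three visits ({18a}).* Harms are not among the listed contents.
- *Outcome lists ({12}).* No harm item. TOR-BSST and the 14-item SWAL-QOL symptom scale bear on swallowing safety at the visit, but neither is a record of events since the last visit.

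An event outside training could therefore reach the record. No stated step asks for it, and none asks for it equally in both arms.

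**Do the safety statements agree?**

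- {11b} and {30}: no important harm from game or measurements.
- {21a}: no data monitoring committee, because serious adverse events are not expected to occur.
- {11b}: early termination for serious adverse events, with aspiration and vomiting as examples.
- {22}: serious adverse events exemplified by fractures and bleeding; aspiration is not named.

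These do not fit together. A provision that turns on aspiration also depends on aspiration being looked for.

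**Context figures.** Inputs: N = 78, allocated 1:1, so 78 / 2 = 39 per arm; 20 sessions of 30 minutes; 8 weeks in total; three assessments.

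- Training time: 20 × 0.5 h = 10 h. Participation: 8 × 7 × 24 = 1,344 h. Share: 10 / 1,344 = 0.7%. Weeks 5 to 8 are 4 / 8 = half of participation and contain no training.
- TOR-BSST administrations: 78 × 3 = 234.
- Expected patients with an event, for assumed 8-week risks of 2%, 5% and 10%: 78 × 0.02 = 1.6, 78 × 0.05 = 3.9, 78 × 0.10 = 7.8. Per arm of 39: 0.8, 2.0 and 3.9.
- Power to detect a halving of the risk p with 39 per arm, two-sided 5%, normal approximation: Φ[(p/2 − 1.96·SE₀)/SE₁], with SE₀ pooled and SE₁ unpooled. For p = 0.10: SE₀ = √(2 × 0.075 × 0.925 / 39) = 0.0596 and SE₁ = √((0.09 + 0.0475) / 39) = 0.0594, which gives about 13%. The same formula gives about 8% at p = 0.05 and 6% at p = 0.02.
- Zero events in 39 leaves a one-sided 95% upper bound of 1 − 0.05^(1/39) = 7.4%.

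The 0.7% is the share of time spent in training, not the adverse event window. The 7.4% follows from the arm size and would be the same under perfect collection. Neither measures the gap. They show only how little of the trial the concrete steps cover, and that a formal comparison of arms is out of reach.

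**The case against.** The best reply is that the article does provide for harms. The opening sentence of {22} is unrestricted, {11b} treats aspiration as a serious adverse event, and {18b} has the researcher follow participants' status after training ends. Section {18a} concerns outcome assessment and harms have their own section. Its list is also not exhaustive, since adherence is an outcome and is missing from it too. Table 1, the CRF and the adverse event form are not shown, and an article may leave solicited items and tabulation by arm to them.

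Most of this stands, and it rules out three stronger readings.

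- A reader might infer that aspiration pneumonia would not be captured, or that all harm collection is confined to sessions. The documents do not support that, because {22} allows an event to be recorded at any time.
- A reader might infer that harms are absent from the three visits. With Table 1 missing and a list that is not exclusive, this cannot be confirmed.
- A reader might infer that a FOIS gain could not be told apart from less safe feeding. TOR-BSST, given at the same visits by a blinded assessor, and the SWAL-QOL symptom scale bear on that question, although they do not count events. The 234 tests are given by an experienced occupational therapist, so they are not unobserved.

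The reply does not supply active ascertainment, equal in both arms, outside training. It also leaves the conflict between {11b}, {30}, {21a} and {22} untouched. That conflict lies in what the article states, not in what it omits.

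**Conclusion.** The point holds as a cheap improvement. The article promises adverse event documentation. It states no active step, the same in both arms, to ascertain aspiration or aspiration pneumonia outside training, including weeks 5 to 8. On the text shown, such events would be recorded only passively in a trial without participant or therapist blinding, and FOIS would lack a comparable record of them by arm.

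No planned figure changes. With 39 per arm and assumed 8-week risks of 2% to 10%, about 0.8 to 3.9 patients per arm would have an event, and power to detect a halving is about 6% to 13%. The gain is a fair description, not a test. The risk range is an assumption, and the conclusion does not depend on it. It does assume that Table 1, the CRF and the full protocol do not already contain these items. If they do, what remains is to reconcile the safety statements.

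**What to change.** - At the existing week 4 and week 8 visits, add the same CRF items in both arms: aspiration event, clinician-diagnosed pneumonia or chest infection, and hospital transfer or death, each since the last visit.
- Have the research coordinator, not the blinded assessor, do any extraction from ward records, because those records could reveal the allocation.
- State in {22} that the adverse event form runs from consent to week 8 and covers the visits at which TOR-BSST is given.
- Report, descriptively and beside FOIS, the number of patients per arm with at least one event.
- Reconcile {11b} and {30} (no important harm), {21a} (no serious adverse events expected), the termination provision in {11b} (aspiration, vomiting) and the examples in {22} (fractures, bleeding). Which clinical rule should apply is for the investigators to settle.

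The cost is a few CRF items, one descriptive table and some redrafting. No new visit or procedure is needed. Visits become slightly longer, and record extraction must be kept apart from blinded assessment.

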### Plans to promote participant retention and complete follow-up {18b}

During the recruitment process, participants will receive information about the study design and requirements. The researcher will explain to participants the benefits and implications of participating in the study and emphasize the importance of completing the study. Participants are permitted to withdraw from the study at any time during the study. Throughout the follow-up period, the researcher will monitor the participant's status at all times and contact the participant as necessary to complete the study. If participants withdraw from the study, efforts will be made to collect data on outcomes up to the time of withdrawal, with the participant's consent.

### Data management {19}

Participant data will be collected through the CRF. Protected folder will be backed up once a month. Informed consent and trial end date will be recorded in the patient dossier. All changes made to the raw data and all steps taken in the analysis will be recorded in the CRF and IBM SPSS. All study data, including patient information, will be archived for 10 years after the end of the study.

### Confidentiality {27}

All data in this study will be anonymized and strict confidentiality measures will be taken. Access to participant data will be restricted to authorized members of the research team and the Ethics Committee of The Hong Kong Polytechnic University. To enhance participant confidentiality, each participant will be provided with a unique trial identification number and his/her details will be securely stored in a protected database at The Hong Kong Polytechnic University. Access to the dataset will be strictly controlled and will only be granted to the research team and the sponsoring organization. It is important to note that participant identification details will not be reported in any publications or studies. In addition, the possibility of sharing anonymized trial data with other researchers for international prospective meta-analyses will be carefully considered, and appropriate measures will be taken to protect participant privacy and confidentiality, such as thoroughly de-identifying all direct identifiable information of participants before data sharing, and processing indirect identifiable information that may contain sensitive information, such as date of birth, by keeping only the year or age, in order to protect the privacy and confidentiality of participants.

### Plans for collection, laboratory evaluation and storage of biological specimens for genetic or molecular analysis in this trial/future use {33}

N/A: There are no biological samples in this study.

## Statistical methods

### Statistical methods for primary and secondary outcomes {20a}

An intention-to-treat analysis will be performed, and the last available measurement will be used when data were lost due to dropout. Statistical analysis will be performed using SPSS 29.0. Statistical significance of all outcome variables will be established at *P* < 0.05.

All continuous data will be tested for normality, and nonparametric tests will be used for non-normally distributed data. Data conforming to normal distribution will be expressed as mean ± standard deviation (SD), and data with non-normal distribution will be expressed as median (interquartile range).

Comparisons of continuous data of two groups at the same time will be analyzed using independent samples t tests or rank sum tests, and comparisons of two groups of rates will be performed using chi-square test or Fisher exact test [31].

Comparison of continuous data trends over time between different groups at different times, if data normality is present, we will perform a series of repeated measures analysis of variance (ANOVA) for each outcome measure to assess differences between time (4 weeks and 1 month post) and between study groups, as well as interactions between time and study groups. For these analyses, the assumptions of sphericity and homogeneity of variances are tested using Mauchly and Levene tests [32]. If the assumption of sphericity is violated, the Huynh–Feldt correction is applied [32].

If the normality assumption is not met, the linear mixed model will be used for analysis, the comparative analysis at each time was performed using the nonparametric statistical Mann–Whitney U test and its own control two-way comparison using the nonparametric statistical Kruskal–Wallis rank sum test [33].

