## Objectives {7}

This study aimed to investigate the effect of video-game on swallowing function in patients with dysphagia through a randomized controlled trial. It is hypothesized that video-game based intervention will improve swallowing function better in patients with dysphagia compared to conventional dysphagia training.

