### Sample size {14}

The sample size was calculated from a previous study conducted by Park et al. [29] in dysphagia patients, which measured patient swallowing function on the Functional Oral Intake Scale (FOIS), with mean of 5.40 and 4.40, SDs of 1.70 and 0.80 for the intervention and control groups, respectively. For a significant level of 0.05 and power of 90%, 31 participants were estimated in each group (62 participants). Finally, to avoid loss of power due to potential dropout, the sample size was increased by 20% for each group, resulting in a total number of participants of *N* = 78. The sample size was estimated using G-Power 3.1 [30].

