### Methods for additional analyses (e.g. subgroup analyses) {20b}

N/A: No subgroup analyses or adjusted analyses will be performed because they are not part of the planned analyses for this study. The primary analysis is sufficient to address the research question.

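### The repeated-measures time factor is written as the two post-treatment visits, which contradicts the sphericity steps beside it and leaves the group-by-time interaction blind to a benefit that lasts

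*Protocol article*

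**What the plan says.** - Statistical methods {20a}: if the data are normal, each outcome gets a repeated-measures ANOVA "to assess differences between time (4 weeks and 1 month post) and between study groups, as well as interactions between time and study groups".
- Same paragraph: "the assumptions of sphericity and homogeneity of variances are tested using Mauchly and Levene tests", with a Huynh–Feldt correction if sphericity fails.
- Same section, just before: "Comparisons of continuous data of two groups at the same time will be analyzed using independent samples t tests or rank sum tests".
- Same section, just after: if normality fails, a linear mixed model is used, with Mann–Whitney tests at each time. The visits in that model are not listed.
- Plans for assessment {18a}: "Each participant will be assessed individually three times, pre-intervention, post-intervention and follow-up". Outcomes {12} gives the same three occasions.
- Additional analyses {20b}: "No subgroup analyses or adjusted analyses will be performed because they are not part of the planned analyses for this study".
- Objectives {7}: the hypothesis is that "video-game based intervention will improve swallowing function better in patients with dysphagia compared to conventional dysphagia training".
- Sample size {14}: FOIS, "with mean of 5.40 and 4.40, SDs of 1.70 and 0.80 for the intervention and control groups, respectively", 5% significance, 90% power, 31 per group, raised to 78 in total for dropout.

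**The concern.** The bracket gives time two levels, both after treatment. Sphericity concerns the variances of differences between pairs of visits. With two visits there is one such difference, so the assumption holds automatically and neither Mauchly's test nor the correction can have any effect. One part of the paragraph describes two levels and another presupposes at least three. An analyst cannot follow both.

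The choice changes what the tests mean. With two post-treatment levels, the interaction asks whether the arms diverge or converge between week 4 and week 8. It says nothing about whether they separated during treatment. Baseline is also absent from the model altogether: it is not a level of time, and adjusted analyses are ruled out. Yet the hypothesis is about improvement. With three levels the interaction becomes informative, but the group main effect then averages in a visit at which randomisation makes the expected difference zero. The time main effect compares visits, not arms, on either reading.

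**Working it through.** **Inputs.** From Sample size {14}: difference Δ = 5.40 − 4.40 = 1.00; SDs 1.70 and 0.80; n = 31 per group. Pooled SD σ = √[(1.70² + 0.80²)/2] = 1.3285; d = 1/1.3285 = 0.753. The documents give no correlation between visits, so ρ = 0.5 and 0.7 are assumed, with 0.3 as a sensitivity value. Further assumptions: normal data, equal variances, the same correlation between every pair of visits, complete data, and two-sided 5% tests.

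**The plan's own figure.** For two means the noncentrality is Δ/(σ√(2/n)) = 1/(1.3285 × 0.2540) = 2.963 on 60 df. A one-sided 5% test has 90.06% power at 31 per group, which reproduces the 31. A two-sided test has 83.0%. The document does not state sidedness. That is a separate matter, and the two-sided value is used below throughout. Dropout: 31/0.8 = 38.75, so 39 per group and 78 in total, as stated.

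**Interaction, two post-treatment visits.** The contrast is (T8 − T4) − (C8 − C4), where T and C are the arm means at weeks 8 and 4. This equals the arm difference at week 8 minus that at week 4.
- Benefit of 1.0 at both visits: 1.0 − 1.0 = 0. The test rejects at its 5% level whatever ρ is (simulation, 4,000 trials per setting: 4.8% at ρ = 0.5, 4.4% at ρ = 0.7).
- Benefit of 1.0 at week 4 and 0 at week 8: the contrast is −1.0. The SD of a change score is σ√(2(1 − ρ)) = 1.329 at ρ = 0.5 and 1.029 at ρ = 0.7. Noncentralities are 2.96 and 3.83; power is 83.0% and 96.4% (simulation 84.0% and 96.6%).

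**Other tests, benefit of 1.0 at weeks 4 and 8, equal expected baselines.**

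| Test | Formula | ρ = 0.5 | ρ = 0.7 |
|---|---|---|---|
| Week-4 t test | SD σ, Δ = 1 | 83.0% | 83.0% |
| Group effect, two post visits | SD σ√((1 + ρ)/2) = 1.151, 1.225; Δ = 1 | 92.0% | 88.5% |
| Group effect, three visits | SD σ√((1 + 2ρ)/3) = 1.085, 1.188; Δ = (0 + 1 + 1)/3 = 0.667 | 66.3% | 58.5% |
| Interaction, three visits | λ = (n/2)(2/3)/(σ²(1 − ρ)) = 11.71, 19.52; F on 2 and 120 df | 86.6% | 98.1% |

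In the last row, 2/3 is the sum of squares of the arm differences 0, 1, 1 about their mean.

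The three-visit interaction does not separate a lasting benefit from a transient one. For differences 0, 1, 0 the centred sum of squares is again 2/3, so λ and the power are the same (simulation 86.5% and 98.1%).

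**Sensitivity, ρ = 0.3.** Two-visit interaction: 5% for a lasting benefit and 69% for one lost by week 8. Two-visit group effect 95%; three-visit group effect 76%; three-visit interaction 73%.

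**The case against.** A reader might infer that the plan would declare a durable benefit negative and a transient one positive. The documents do not support that. No section makes the interaction the test of efficacy. The ANOVA is introduced for trends over time, and whether the arm difference changes from week 4 to week 8 is a legitimate question about durability. The plan also has between-arm tests at each visit, of the same form as the comparison the trial was sized on, and the two-visit group effect. Both can detect a lasting benefit. Which test decides is something an analysis plan, not shown here, may settle.

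A reader might also infer that the authors meant to exclude baseline. That is not established. The bracket could be a loose list of the post-baseline times, and the sphericity steps point to three levels. On that reading the interaction is well powered. The text still conflicts with itself, and nowhere is the factor restated with baseline in it.

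Finally, FOIS has seven levels and may fail the normality check. The ANOVA would then not be run on it and the figures above would be only a guide. This limits the numbers but does not remove the problem: the mixed model that replaces the ANOVA needs its visits defined too.

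**Conclusion.** The point holds in a limited form. The stated time factor contradicts the sphericity steps in its own paragraph and does not match the three scheduled assessments. Followed literally, the interaction has no power beyond its 5% level for a benefit held from week 4 to week 8, and about 83–97% for one lost by week 8. The zero contrast is algebra and needs no assumption about correlation. The percentages rest on 31 per arm, a difference of 1.0, a common SD of 1.33, normal data and an assumed ρ of 0.5 to 0.7.

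Adding baseline as a level repairs the interaction (87–98%) but weakens the group main effect (about 58–66%), so adding the word is not by itself enough. The defect lies in the interaction as specified and in the absence of baseline from the model. It does not leave the trial unable to detect a lasting benefit: the week-4 test keeps 83% and the two-visit group effect 89–92%.

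**What to change.** - In Statistical methods {20a}, state the visits of the longitudinal model as baseline, week 4 and week 8, for both the ANOVA branch and the mixed-model branch.
- Test the hypothesis in Objectives {7} for FOIS by one contrast: the between-arm difference at week 4, adjusted for baseline FOIS. Report the week-8 between-arm contrast for durability.
- State that the time main effect and the overall group and interaction F tests are not tests of efficacy.
- Amend Additional analyses {20b}, which at present excludes adjusted analyses, so that this baseline adjustment is allowed.
- Keep TOR-BSST as the other primary measure, with its own between-arm comparison. Naming the FOIS contrast must not drop it by silence.

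The cost is protocol and analysis-plan wording. All three visits are already scheduled, and the article places the trial before recruitment. The one loss is that the omnibus F tests give up their role.

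### The non-normal fallback compares a patient's own visits with Kruskal–Wallis, a test for independent samples, names no deciding between-group analysis for FOIS, and sits beside a bar on baseline adjustment

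*Protocol article*

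**What the plan says.** Under Outcomes (item 12), swallowing function is the primary outcome, measured by TOR-BSST and FOIS. On the latter: "FOIS consists of a 7-point scale". The sample size (item 14) rests on FOIS, "with mean of 5.40 and 4.40, SDs of 1.70 and 0.80 for the intervention and control groups, respectively".

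The statistical methods section (item 20a) tests continuous data for normality and promises nonparametric tests where it fails. For comparisons over time it plans repeated-measures ANOVA if the data are normal. Otherwise: "If the normality assumption is not met, the linear mixed model will be used for analysis". The same sentence adds Mann–Whitney U between groups at each time, and "its own control two-way comparison using the nonparametric statistical" Kruskal–Wallis test.

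On additional analyses (item 20b): "No subgroup analyses or adjusted analyses will be performed because they are not part of the planned analyses for this study".

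Item 18a has each participant assessed three times: before the intervention, after it and at follow-up.

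**The concern.** Four features of the text combine.

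- **Wrong test.** A comparison in which patients serve as their own control is paired. Kruskal–Wallis ignores the pairing and treats the visits as separate groups of people. Its p-values are then too large, and modest real change within a group can be missed.
- **Likely route.** A seven-level integer score often fails a normality test, so the branch with this error is the one FOIS will probably follow.
- **No deciding analysis.** A linear mixed model in its usual form assumes normal residuals and random effects, so failed normality is not a reason to move to it. It also sits oddly with the promise of nonparametric tests in the same section. The text does not say whether the mixed model or the Mann–Whitney test answers the primary hypothesis, which leaves a choice that could be made after the results are seen.
- **Baseline adjustment.** Excluding adjusted analyses gives up precision that baseline FOIS, already collected, could supply.

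**Working it through.** **Inputs from the protocol.** FOIS levels 1–7 (item 12). Means 5.40 and 4.40, SDs 1.70 and 0.80, alpha 0.05, power 90%, 31 per group, 78 in total after the 20% dropout allowance, so 39 per group (item 14). Three assessments per patient (item 18a). The protocol gives no between-visit correlation; 0.3 to 0.7 is assumed for the within-group tests and 0.3 to 0.6 for baseline adjustment.

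**Step 1: reproduce the planned size.** Combined SD = √((1.70² + 0.80²)/2) = √1.765 = 1.329, so d = 1.00/1.329 = 0.753. With the noncentral t, 31 per group gives 90.1% power one-sided at 0.05, and 83.0% two-sided. Dropout: 31/0.8 = 38.75, rounded up to 39 per group, or 78. The stated size is reproduced, but only one-sided.

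**Step 2: how likely is the fallback?** Normal draws were rounded and clipped to 1–7, and Shapiro–Wilk was applied to each arm at 5%.

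| Mean, SD | n = 31 | n = 39 |
|---|---|---|
| 5.4, 1.70 (planning) | 98% | 99.9% |
| 4.4, 0.80 (planning) | 99.8% | 100% |
| 4.4, 1.33 (assumed) | 67% | 88% |
| 4.0, 1.70 (assumed) | 46% | 71% |

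Repeat runs differ by a point or two; the two assumed central shapes span about 44–88%.

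**Step 3: Kruskal–Wallis on three visits by the same patients.** The test takes the variance of a difference between two visit means as 2σ²/n. With correlation ρ it is 2σ²(1 − ρ)/n. The statistic therefore behaves roughly as (1 − ρ) times a chi-square on 2 degrees of freedom, and the true rejection rate at nominal 5% is about 0.05^(1/(1 − ρ)):

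- ρ = 0.3: 0.05^1.43 = 1.4%
- ρ = 0.5: 0.05^2 = 0.25%
- ρ = 0.7: 0.05^3.33 = 0.005%

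Simulation with rounded 1–7 scores (n = 39, mean 4.4, SD 1.33) agrees. It runs slightly higher, as expected if rounding lowers the effective correlation.

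| ρ | Null: Kruskal–Wallis | Null: Friedman | 0.4 SD power: Kruskal–Wallis | 0.4 SD power: Friedman |
|---|---|---|---|---|
| 0.3 | about 1.5% | about 5% | 35% | 47% |
| 0.5 | about 0.5% | about 5% | 30% | 60% |
| 0.7 | 0.1% or less | 5–6% | 24% | 82% |

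At a 0.75 SD change (about one FOIS level: 0.75 × 1.33 = 1.0), Kruskal–Wallis power is about 92–98%. Friedman gives about 99% at ρ = 0.5 and almost 100% at 0.7, so little is lost.

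If the comparison is meant for pairs of visits, the fault remains. Null rejection is 2.4%, 0.9% and 0.2% at ρ = 0.3, 0.5 and 0.7. Power at 0.4 SD is 38%, 35% and 33%, against 51%, 62% and 81% for Wilcoxon signed-rank.

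**Step 4: between-group tests under the null.** With 39 per group on rounded scores (mean 4.4, SD 1.33 in both), Mann–Whitney rejects in 4.9% and the t test in 5.0%. Both hold their level.

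**Step 5: what a baseline covariate is worth.** Adjustment multiplies the SD by √(1 − ρ²), with ρ now the correlation of baseline with week 4. At 31 completers per group, two-sided 0.05:

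| ρ | Adjusted SD | Power |
|---|---|---|
| none | 1.329 | 83% |
| 0.3 | 1.267 | 86% |
| 0.4 | 1.218 | 89% |
| 0.5 | 1.151 | 92% |
| 0.6 | 1.063 | 95% |

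If all 39 per group complete, unadjusted two-sided power is already 90.7%.

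**The case against.** The best defence is that the trial's hypothesis is between groups, and the same sentence supplies Mann–Whitney at each visit, a legitimate rank test for an ordinal score. A reader might infer that the primary comparison is invalid or its false-positive rate inflated; step 4 does not support that. The Kruskal–Wallis error is conservative and confined to within-group comparisons. It also matters little for large changes, so a claim that most real change would be missed holds near 0.4 SD but not near 0.75 SD.

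Nor is it certain that FOIS fails the normality test. That is nearly so at the planning values, less so for central, wide distributions.

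The case against the linear mixed model should not be pushed too far either. With about 39 per arm and a bounded score, mean-based inference is serviceable, and a mixed model with robust standard errors is one acceptable remedy. An ordinal model is a preference, not a required correction.

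On baseline, a reader might infer that the information is discarded altogether. The text does not establish this. The ANOVA time factor lists only the two later assessments, but baseline could still enter the mixed model as a visit, and the bar on adjustment sits under additional analyses. Omitting a covariate costs efficiency; it is not an error. The gain depends on an assumed correlation and on 31 completers per group.

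What stands: Kruskal–Wallis is the wrong test for paired data, the fallback names no deciding analysis, and the exclusion of adjusted analyses is worded broadly enough to cover a baseline covariate. These are stated choices, not details left to an analysis plan.

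**Conclusion.** The point holds and should be fixed. Applying Kruskal–Wallis to a patient's own visits is wrong as written, and this does not depend on the simulations; only the size of the effect rests on the assumed correlation and the rounded-normal score model. The normality switch will probably send FOIS down this branch. There the reason for moving to a linear mixed model does not hold, and the analysis that decides the primary hypothesis is not named. The exclusion of adjusted analyses forgoes roughly 3 to 12 percentage points of two-sided power at 31 completers per group (83% to 86–95%) under assumed correlations of 0.3 to 0.6. The documents do not support a conclusion that the between-group comparison is invalid.

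**What to change.** 1. In item 20a, replace Kruskal–Wallis for within-group comparisons by Friedman across three visits, or Wilcoxon signed-rank for pairs of visits.
2. Drop the normality-test switch for FOIS. Name one between-group analysis at week 4, adjusted for baseline FOIS, as the deciding one: for example, a baseline-adjusted mixed model with robust standard errors. A proportional-odds model is an option. Mann–Whitney can remain as a supporting analysis.
3. State how the baseline visit enters the model.
4. Amend item 20b to allow adjustment for the baseline value of each outcome.

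The cost is wording only. No extra patients, visits or measurements are needed, and the article describes the trial as not yet recruiting. If the ordinal model is chosen, the odds ratio is somewhat harder to explain than a mean difference.
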